**1.3. Financing**

'Unrestricted grant' from Eli Lilly Denmark. The Psychiatric Research Unit thus has sole responsibility for the trial and is both Sponsor and Investigator as far as GCP (Good Clinical Practice) is concerned. Applications for further grants will be made.

**1.12. Study site**

Psychiatric Hospital/Frederiksborg General Hospital, [name], Denmark, [contact], [contact].

The Psychiatric Department of Hvidovre Hospital may join the study later and a protocol amendment will be written accordingly and sent to the Danish Medicines Agency and the Scientific Ethics Committee. For this reason the study protocol has been submitted not only to Frederiksborg County, but also to the communities of Frederiksberg and Copenhagen (an entity as far as the Ethics Committee is concerned) for approval.

**1.13. Laws and requirements**

The study will be performed according to the protocol and the valid Danish laws and requirements.

**2. BACKGROUND INFORMATION**

Despite the development of new antidepressants, patients with both unipolar and bipolar depression suffer from continued episodes of depression (Kennedy et al. 2003). New methods are therefore asked for to bring these episodes to an end within a short time (Kessing et al. 2004, Bech et al. 2005) in order to reduce the period of time in which the patients are depressed and the number of suicides

(Sokero et al 2005). In the following the various elements pertinent to the investigation will be described.

**2.1. Antidepressants**

All patients will receive the antidepressant duloxetine. Duloxetine has recently been approved by the Danish Medicines Agency. Among the drugs having an effect on both types of transmitters (SNRIs) this drug has been selected because it has a balanced re-uptake inhibition of both serotonin and noradrenalin. In regard to effect, duloxetine is related to venlafaxine which also is an SNRI. Venlafaxine, which is used frequently in the treatment of hospitalised patients with depression, requires a fairly high dosage before the noradrenalin reuptake inhibition starts operating. In the dose range of 40 to 120 mg/daily, duloxetine has shown a dose-response correlation with a minimal effective dose of 60 mg.

**2.2. Sleep deprivation (wake therapy)**

Sleep deprivation is a well-known method, which in numerous studies has proved its ability to eliminate or reduce the severity of the depression within just a few hours (Ostenfeld 1973, Ostenfeld 1986, Kuhs and Tölle 1991, Smeraldi 1999, Benedetti 2001). Several Danish studies have confirmed this effect (Svendsen 1976, Larsen et al., 1976, Kvist et al. 1980). Sleep deprivation can be carried out in several ways. In partial sleep deprivation the patient is waked up at 2.30 a.m. In the following the patient has to stay awake for the rest of the night and all next day and is not allowed to go to sleep again until the following night (Schilgen et al. 1987). In total sleep deprivation, the patient is awake all night and the following day. The most recent sleep deprivation regimens require that the patient goes through 3 partial or total sleep deprivations in the course of one week, but always with one regular night of sleep to follow one night of sleep deprivation.

In older days, sleep deprivation was quite well-known and senior nursing staff and doctors can describe how many institutions used sleep deprivation in the treatment of depression. We don't know precisely why the method has been abandoned, but it is only used sporadically in Denmark nowadays. The method is used routinely in a number of countries, among them Germany, Austria and several locations in the USA. The development of pharmacological treatment methods in beginning of the 1950s and faith in the effect of these new drugs is probably one of the reasons for the abandonment of sleep deprivation. However, a continued interest in sleep deprivation can be documented by the large number of publications about the method. When we made a search National Library of Medicine’s ”PubMed" in the beginning of 2005, the number of titles referring to depression and sleep deprivation was 622. 112 of these had appeared after the year 2000, and 20 had been published within the last calendar year.

The essence of the published results is that approximately 60-70% of all patients with major depression respond well to one night's sleep deprivation, i.e. the degree of their depression is reduced by 50% or more (response), and a number of patients will even be without any symptoms of depression (remission) (Wirz-Justice et al. 1999, Wirz-Justice et al. 2004).

Patients whose depression is part of a bipolar illness often experience a better effect from sleep deprivation than patients whose depression is part of a unipolar depression. Clinical experience has shown that bipolar as well as unipolar patients without significant personality disorders and patients with large day-to-day variations within their depressive condition achieve the best treatment results. Bipolar as well as unipolar depression fulfilling these criteria (no significant personality disorder or large variations) experience an equal gain from both SSRIs, SNRIs (Goodwin 2003) and lithium (Bech et al. 1980).

Patients who experience a large day-to-day variation in depression severity have a serious social handicap, because planning ahead – activities and work - is very difficult for them due to their unstable condition. On average, patients with bipolar depression do not only experience a larger number of episodes than those with unipolar depression (Angst et al. 2003), but also a continued risk of new episodes, maybe even an increasing risk as they grow older (Kessing et al. 2004, Keller 2004, Bech et al. 2005). These patients are therefore natural targets for new treatment methods. Sleep deprivation and the day structure they are asked to maintain afterwards hopefully can be an instrument they can use on their own initiative to fight an illness which is recurrent for many of them.

Mostly (but not always), the effect of one night's sleep deprivation is short, and most patients will be back in their depressive condition after the following night's sleep. To overcome the brevity of the effect and the relapse to the previous condition, several methods have been developed:

- The simplest method is repeated sleep deprivation a number of times, resulting in a continued effect and an increased duration. Most centres use 3-6 sleep deprivations. This increased effect by repetition is well-known from other treatments, e.g. ECT (Electro Convulsive Treatment).
- Light therapy is used at the end of the sleep deprivation night (for 30 minutes at 4.00 a.m.), partly to reduce tiredness (Colombo et al. 2000, Benedetti et al. 2001, Fritzsche et al. 2001, Neumeister et al. 1996) and partly as a daily therapy at mornings, possibly as long-term treatment, thus implying that the patient continues with it after discharge from hospital (Martiny 2004, Benedetti et al. 2003). Light therapy is used irrespective of season.

Sleep-phase-advance, in which the patient goes to sleep early and is woken-up early, i.e. the patient's diurnal rhythm is "advanced" compared to the usual pattern of sleep. Several studies have shown that ”sleep-phase-advance” in itself has had an effect similar to partial or complete sleep deprivation (Voderholzer 2003, Berger 2003). In this study, sleep-phase-advance is used in a version modified according to the possibilities of a psychiatric ward and where the aim is to maintain the improvement that has been obtained by sleep deprivation.

- Trials with pindolol (β-blocker usually used to treat high blood pressure) as an addition to sleep deprivation have shown that patients treated with pindolol experienced a better antidepressant effect and fewer relapses than the control group which solely received sleep deprivation (Smeraldi et al., 1999).
- Trials with lithium (mood stabiliser) showed that this drug was able to enhance and maintain the effect of sleep deprivation (Szuba et al. 1994, Benedetti et al. 2001).

Sleep deprivation must always be followed by a night of normal sleep (recovery sleep). Patients receiving sleep deprivation are usually hospitalised, but some patients use the method at home after sleep deprivation at a hospital or clinic (Loving et al. 2002).

The risk of switching into a manic episode after sleep deprivation is of the same magnitude as for antidepressants (Colombo 1999). No excessive frequency of suicide has been seen after its use (Vovin Ria et al. 1985, Kuhs et al. 1991).

Clinical experiences with sleep deprivation show a lower effect in patients who have not responded to long-term pharmacological treatment with several antidepressants with varying mechanisms of action (refractory depressions).

**2.3. Exercise**

Exercise has shown to have an impact on the diurnal rhythm of healthy study subjects (Buxton et al. 2003) and several randomized trials of the effect of exercise on depression are currently ongoing. It is expected that the effect of exercise on depression has a slower onset of action than the effect of sleep deprivation (Blumenthal et 1999, Babyak et al 2000) and that there will be a connection between the degree of exercise (intensity and stamina) and the development of the degree of depression. Therefore, exercise is a good alternative to sleep deprivation and has therefore been chosen as part of the treatment in the non-sleep deprivation group (group B). The exercise programme is to be commenced during hospitalisation. The intensity of the exercise is adapted to the single patient, but 30 minutes daily are aimed at, as recommended in the 2004 campaign by the National Health Board (Sundhedsstyrelsen 2004). The patients continue doing their exercises throughout the study period and compliance is monitored at each visit by means of interview forms and exercise diaries.

**3. OBJECTIVE**

The main objective of the trials is to examine whether sleep deprivation in combination with light treatment, duloxetine and maintenance of diurnal rhythm (Group A) is able to induce a faster onset of action and lasting antidepressive response compared to an individually designed exercise programme in combination with treatment with duloxetine (Group B).

Secondary objectives are studies of cortisol concentration, variability of the degree of depression, the idiographic method and finally, applicability and effect of exercise over 9 weeks under supervision. The following hypotheses ar going to be tested in the study:

- Is sleep deprivation in combination with duloxetine, light and maintenance of diurnal rhythm (Group A) able to induce a greater degree of response or remission than exercise in combination with duloxetine (Group B). The hypothesis is tested after 2, 9 and 29 weeks of therapy?
- Is it possible for patients with major depression during the supervised course of treatment of 9 weeks to achieve the National Health Board's recommendation of exercising 30 minutes per day, and is there any association between the exercise effort and the degree of depression after 29 weeks?
- Is the cortisol concentration as measured in urine and saliva the beginning of week 2 correlated to the severity of depression as measured after 2, 9 and 29 weeks of therapy?
- Is the concentration of cortisol measured in saliva correlated with the concentration of cortisol in diurnal urine?
- Is the idiographic method more sensitive to change of degree of depression than clinician- and patient-rated scales and questionnaires for depression?
- Can variability in the degree of depression as measured with the Preskorn scale (see psychometrics) predict response to sleep deprivation?

**4. STUDY PLAN AND DESIGN**

**4.1. Study structure**

The study examines the difference between antidepressant effect of two different chronobiological principles in patients with major depression treated with duloxetine (A and B). The trial has the design of a controlled clinical trial, in which the patients are randomised to either one of the two treatment groups (A or B). The study is single-blind, as the rater of the severity degree of depression (Hamilton scale) is blinded towards the treatment group to which the interviewed patient belongs.

4.1.1. Blinding procedures

It is not possible to blind the patient towards type of treatment (sleep deprivation or exercise). It is, however, possible to blind a permanent rater towards the treatment the patient has received. This can be done by having a rater who interviews and rates the patient each time throughout the whole study period by means of the Hamilton scale. The patients will be informed that they are not to disclose the type of treatment they receive to this permanent rater who assesses severity of depression according to Hamilton. There is no item in the Hamilton scale to reveal the type of treatment the patient receives, not even the sleep item, as all patients record their sleep in a sleep diary. The rater who conducts the interview will not meet the patient in the ward, as the regular visits are outside (before and after) the period of hospitalisation and will not be permitted to see patient records or CRFs. This rater will only receive the Hamilton rating sheet which does not contain information as to treatment group. All other procedures of the study will be performed by unblinded evaluators.

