4.1.4. Hospitalisation phase: week 1 (7 days)

All study participants are hospitalised and meetings with the study investigators are envisaged for each working day. All patients (both groups, A and B) are hospitalised in an open in-patient ward. See Figures 1 and 2. Previously hospitalised patients can be discharged if their condition permits it. Patients admitted due to study participation will be discharged 6 days after admission unless their condition does not allow it. If the patient stays in hospital the trial will follow the usual guidelines, but the visits will take place in the in-patient ward whenever necessary.

Group A

- During hospitalisation, Group A patients go through 3 sleep deprivations, the first one on the day of admission (see Figure 2). Sleep deprivation is mainly carried out as total sleep deprivation, i.e. the patients stay awake all night. However, in some cases partial sleep deprivation may be used, in which the patient is woken up at 02.00 a.m. and has to stay awake for the remains of the night. This can be done either due to an individual patient evaluation made by the investigator or due to a wish on the part of the patient. There may be good reason for using partial sleep deprivation in case of medical diseases such as diabetes, where the blood sugar level can get out of balance, or in other diseases that may be influenced by a longer wake period. Also elderly patients expect not to be able to stay awake all night may also profit from partial sleep deprivation. Patients who experience that their first and total sleep deprivation is too demanding may also switch over to partial sleep deprivation. A combination of total and partial sleep deprivation is thus permitted.
- In the evening after each sleep deprivation the patients must go to bed at 9 p.m. at the very latest and get up at 7 a.m. the following morning (sleep-phase advance).
- The treatment with duloxetine continues unchanged, with a dose of 60 mg daily.
- The patients are informed about light treatment on the day of admission which is given for the first time the following morning and subsequently each day of the study period. The duration of light treatment is 30 minutes. The time of day of the light treatment is decided after completion of the MEQ questionnaire (see psychometrics paragraph). In addition to this, to fight tiredness, the patients take light treatment at 4 a.m. each night during the period of sleep deprivation.

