4.1.5. Follow-up period I: week 2 until week 9 (included) (7 weeks)

During this phase the patients are examined weekly.

Group A

- Patients with scores of 8 or more on the Hamilton Depression Scale at visit 4, 5 or 6 will be offered two additional – either total or partial - sleep deprivations in the week of their visit. If practical reasons prevent this, the two sleep deprivations can be performed in the following week. Both sleep deprivations must be performed during the same week (preferably Tuesday and Thursday). The patients should be admitted in the evening, preferably Tuesday for the first and Thursday for the second sleep deprivation. The patients stay awake during the night in the ward and can be discharged next morning. No further sleep deprivations are permitted during the remaining study period and they are not allowed to carry out sleep deprivation on their own at home at any time.
- Duloxetine treatment is continued with an unchanged daily dose of 60 mg.
- Light treatment at home is continued, with daily treatments as in the previous study phase. The patients can borrow the lamp from the hospital.
- Patient education concerning maintenance of diurnal rhythm is on a continuous basis, at each visit, with an envisaged bedtime at 11 PM and a wake-up time at 8 AM at the very latest.
- The patients are instructed on a continuous basis how to fill in medication diary, light diary and sleep diary.

Group B

- Duloxetine treatment is continued with an unchanged daily dose of 60 mg.
- The patients receive weekly instructions and training within their individual exercise program. The time at which the patients have to show up should as far as possible be coordinated with the other visits to the hospital.

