**4.2. Psychometrics**

To make a diagnosis, to examine co-morbidity and possible exclusion diagnoses the M.I.N.I. (Mini International Neuropsychiatric Interview) (Sheehan et al. 1998) and the SCID (First, 2002) will used, both based on the American DSM-IV diagnostic system (APA 1994). DSM-IV also contains the ”Seasonal Pattern Specifier” we use for the diagnosis of winter depression (”Seasonal Affective Disorder”). To elucidate atypical depression, the DIAD (Diagnostic Interview for Atypical Depression) (Terman et al 2003) is used.

Patients with personality disorders are identified and excluded by means of the SCID (First, 2002). DSM-IV subclassifies major depression into ”Major depressive disorder, single episode” (296.2) and ”Major depressive disorder, recurrent” (296.3). Bipolar disorder is first classified by using the M.I.N.I. criteria for ”previous hypomanic/manic episode”, and patients fulfilling the diagnostic criteria for previous manic or hypomanic episode are then subdivided according to DSM-IV into the diagnostic codes ”Bipolar I disorder, most recent episode depressed” (296.5), ”Bipolar I disorder, most recent episode unspecified” (296.7), and "Bipolar II disorder" (296.89).

For the assessment of severity of depression clinician-rated as well as self-rating scales are used.

The clinician-rated scales are the 17-item Hamilton Depression Scale (HAM-D17),(Bech et al. 1986), the Melancholia Scale (MES) (Bech 2002a), and a Hamilton Depression 6-item subscale (HAM-D6), (O'Sullivan et al. 1997, Licht et al. 2005). Sleep studies usually use the HAM-D6, as it has no sleep item. During hospitalisation, the patients are assessed daily with the HAM-D6. During hospitalisation, patient assessments are made daily with HAM-D6. A minimum score of 13 on the 17-item Hamilton Depression Scale has been chosen for inclusion, as some patients with long term depressions have scores on this moderate level, which, however, has a marked impact on social functioning and quality of life. This is owing to the peripheral depression symptoms which still are present. Another reason is that one single measurement may be unreliable in patients with great day-to-day variability of the degree of depression. It has also been demonstrated that the effect of antidepressant treatment starts at this level (Paykel 1990).

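### The protocol wrongly says the Hamilton sleep item cannot reveal treatment because every patient keeps a sleep diary; asking about sleep can disclose Group A to the only blinded assessor

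*Protocol*

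**What the plan says.** Section 4.1 bases the blinding of the trial on one role: "The study is single-blind, as the rater of the severity degree of depression (Hamilton scale) is blinded". Section 4.1.1 describes this as "a rater who interviews and rates the patient each time throughout the whole study period by means of the Hamilton scale", and leaves all other procedures to evaluators who know the allocation. On the content of the scale it says: "There is no item in the Hamilton scale to reveal the type of treatment the patient receives, not even the sleep item". The reason follows in the same sentence: "not even the sleep item, as all patients record their sleep in a sleep diary".

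The other safeguards in 4.1.1 are an instruction to patients not to disclose their treatment (repeated in 4.6.2), no meeting between rater and patient on the ward, no access to records or CRFs, and a rating sheet that does not show the group.

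Sleep differs between the groups by design. Section 4.1.4 says that "Group A patients go through 3 sleep deprivations" while in hospital, mainly as total deprivation with partial deprivation permitted. Under 4.1.5, Group A patients scoring 8 or more at visit 4, 5 or 6 are offered two further nights: "The patients stay awake during the night in the ward and can be discharged next morning". Visits in that period are weekly. Section 4.3.1 makes HAM-D17 response or remission at weeks 2, 9 or 29 the primary efficacy parameter. On the choice of scale, section 4.2 remarks: "Sleep studies usually use the HAM-D6, as it has no sleep item".

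**The concern.** The diary is the only reason given for treating the sleep item as harmless, and it does not address the problem. What could unblind the rater is the content of the patient's answer, not where else the patient writes it down. If the rater asks about sleep, a Group A patient may have whole or part nights awake to report, in a pattern that Group B lacks. If the rater scored the item from the diary instead, the diary would show the same nights.

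The remaining safeguards do not cover this route. The non-disclosure instruction stops a patient from naming the treatment, but here the scale itself asks about the treatment's most visible feature.

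The stake is the primary endpoint. Patients and all other evaluators know the group, so the blinded Hamilton rating is the only protection against assessor bias. The concern is not the few points the sleep items add to the total. A rater who has guessed the group may score every item differently, and the same rater continues to week 29.

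**Working it through.** **1. Does the stated reason support the statement?** Compare the groups on what a sleep question can bring out.

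| | Group A | Group B |
|---|---|---|
| Sleep diary | yes | yes |
| Deprivation nights, hospital week | 3 (one may be skipped, 4.6.6) | 0 |
| Further deprivation nights, follow-up period I | 0 or 2 | 0 |
| Deprivation nights after that | none permitted | 0 |

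The first row is the reason the protocol gives. The next two rows are what an answer about sleep would reflect. Equality in the first row says nothing about them.

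**2. How much could the week-2 interview reveal?** This depends on the recall window, which the protocol does not state. Figure 2 gives an example week: deprivation on Monday, Wednesday and Friday, each followed by a sleep-phase-advance night, with discharge on Saturday. Assuming that pattern, count the deprivation nights inside the window:

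| Week-2 visit on | Last 1–2 nights | Last 3–4 | Last 5–6 | Last 7 |
|---|---|---|---|---|
| Monday | 0 | 1 | 2 | 3 |
| Friday | 0 | 0 | 0 | 1 |

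Exposure therefore ranges from none to all three nights. The Tuesday and Thursday pattern preferred for the additional nights behaves in the same way. At a Monday visit the week after, a seven-night window holds both nights and a three-night window holds neither.

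**3. The plan's own figures.** Section 11 gives means of 10 (A) and 13 (B) at week 9, SD 4, type-I error 0.05, power 0.90 and 39 per group. The two-sided normal formula gives n = 2 × (1.960 + 1.282)² × 4² / 3² = 37.4, rounded up to 38. The t-based solution is 38.35, rounded up to 39. The stated figure reproduces. Section 12 plans 50 per group.

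**4. Illustration of what a lost blind could do.** Assume no true difference, SD 4, 50 per group, and a constant shift of b points in favour of Group A. Neither the size nor the direction of b comes from the protocol.

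- *Mean comparison.* SE = 4 × √(2/50) = 0.8. False-positive rate = 1 − Φ(1.96 − b/0.8) + Φ(−1.96 − b/0.8). For b = 1: 1 − Φ(0.71) + Φ(−3.21) = 0.24.
- *Response chi-square.* Entry score fixed at 24, so response is a score below 12. With a common true mean of 13, apparent response is Φ((12 − 13 + b)/4) in A and Φ(−1/4) = 0.401 in B. The rejection rate sums exact binomial probabilities over all outcomes with Pearson chi-square above 3.84.

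| b | Share of planned 3 points | Response A vs B | Chi-square false-positive rate | Mean comparison false-positive rate |
|---|---|---|---|---|
| 0 | 0% | 0.40 vs 0.40 | 0.05 | 0.05 |
| 0.5 | 17% | 0.45 vs 0.40 | 0.08 | 0.10 |
| 1 | 33% | 0.50 vs 0.40 | 0.18 | 0.24 |
| 1.5 | 50% | 0.55 vs 0.40 | 0.34 | 0.47 |
| 2 | 67% | 0.60 vs 0.40 | 0.53 | 0.71 |

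With a common mean of 11.5 the chi-square column becomes 0.06, 0.08, 0.17, 0.31 and 0.49. A continuity correction lowers it; with mean 13 it is 0.03, 0.06, 0.13, 0.27 and 0.45. These use week-9 inputs because the protocol gives no means for week 2.

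**The case against.** The best reply is that the protocol does not show the blind failing. The Hamilton form is an enclosure, and its recall window and scoring rule for sleep are not in the text. Every deprivation night is followed by a night of sleep, so a short window might contain no deprivation night at all. Partial deprivation means being woken at 02.00, which can sound like early waking. One of the three nights may be skipped. Poor sleep is common among depressed inpatients in either group. Patients are told twice not to disclose their treatment and may describe their usual sleep without mentioning nights kept awake. After follow-up period I, sleep answers carry no new signal, so any effect at week 29 rests on an earlier guess being retained.

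All of this stands as a limit on extent. A reader might infer that the sleep item necessarily identifies every Group A patient, and the documents do not support that. None of it rescues the statement in 4.1.1, which is absolute and rests on the diary alone.

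The diary sentence could also mean that sleep is scored from the diary, outside the rater's interview. That would be close to the remedy below. But 4.1.1 does not say who would do the scoring, and it describes the rater as completing the Hamilton rating. On this reading too the text needs correcting.

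Two further inferences should be resisted. A reader might apply the week-9 mean of 10 and SD 4 to visits 4–6 and conclude that most of Group A is re-exposed. The protocol gives no means for those visits, and the extra nights are only offered. A reader might also take the false-positive rates as estimates for this trial. They rest on an invented constant shift in every Group A patient, always in the same direction.

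**Conclusion.** The statement that the sleep item cannot reveal treatment is wrong as reasoned. Only Group A has deprivation nights, and no stated safeguard covers a truthful answer to a question about sleep. Such questions can reveal allocation to the only blinded assessor, most clearly at week 2 and at visits after additional deprivations. The permanent-rater arrangement lets a correct guess persist to weeks 9 and 29.

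The extent is unknown. In the Figure 2 example the week-2 interview could cover anywhere from none to all three deprivation nights, depending on the recall window and the visit day. The consequence is likewise conditional: an assumed 1-point shift, one third of the planned difference, would take the false-positive rate to about 0.17–0.18 for the response chi-square and 0.24 for a mean comparison. The point rests on the protocol's own contrast between the groups and does not depend on those rates. Because a blind once lost cannot be restored, the correction belongs before the first rating.

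**What to change.** - Delete the statement in 4.1.1 that the sleep item cannot reveal treatment.
- Instruct the blinded rater not to ask about sleep at any visit.
- Have unblinded staff score the sleep items from the diary on a separate sheet, by a fixed written rule that states the recall window and how deprivation nights are handled. Form the HAM-D17 total at data entry, so that the rater never sees the sleep scores.
- Add a sensitivity analysis of the primary comparison on blinded items only: the HAM-D6, or the HAM-D17 without its sleep items.
- Record the rater's guess of group, which also captures cues from conversation about light, tiredness or exercise that this change does not remove.
- Reconcile 4.1.1, which places the rater's visits outside the hospital stay, with Flowchart 1, which marks the Hamilton at visit 2 in the hospital week.

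**Cost.** One extra sheet, a scoring rule and some wording; the HAM-D17 endpoint definitions are unchanged. The real downside is that the sleep items within the primary total are then scored by staff who know the group. Scoring from a diary by rule limits the room for judgement, and the blinded-items analysis checks whether the result depends on those items.
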